### Recruitment {15}

This is a nationwide multicentric study that will recruit at least 750 participants from Beijing Tiantan Hospital, China-Japan Friendship Hospital, The Second Hospital of Tianjin Medical University, Taiyuan Central Hospital of Shanxi Medical University, Linfen Fourth People’s Hospital, Shandong Provincial Hospital, Qingdao Municipal Hospital (Group), Huai’an Second People’s Hospital, The First Hospital of China Medical University, The Second Affiliated Hospital of Zhengzhou University, Fujian Provincial Hospital, Cangzhou Central Hospital, The People’s Hospital of Fujian Province, Beijing Tsinghua Chang Gung Hospital, Peking University International Hospital, Tianjin First Central Hospital, Tianjin Huanhu Hospital and Baoding First Central Hospital in 10 provinces and cities in China. Patients presenting to the Department of Emergency, Dermatology, Neurology or Pain Management at the aforementioned participating centres will be screened for eligibility.

Prior to the initiation of the study, research assistants (at least 2 research assistants per centre) will be trained regarding the details of this study protocol, to ensure smooth operations and consistency. Patients aged more than 50 years who are diagnosed with uncomplicated HZ, who present with vesicles within 72 h of their emergence, and have an average pain score of at least 40/100 mm on a visual analogue scale will be considered for enrollment. The research assistants will be informed and asked to screen patients for eligibility. Eligible patients who are willing to participate will be provided with a verbal explanation of the written consent. Patient queries will be answered and each patient interested in the study will have sufficient time to decide whether to participate in this study, and informed consent will be obtained from willing participants.

### Assignment of interventions: allocation

#### Sequence generation {16a}

After signing the written informed consent, participants will be randomized for allocation. Randomization will be performed using a web-based central randomization system with permuted blocks by an independent research assistant. Participants will be assigned to either the duloxetine arm or the control arm in an allocation ratio of 1:1. Given the open-label nature of this study, the patients, physicians and research team will inevitably be aware of the allocation. However, the outcome assessors will be blinded to the intervention.

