### Trial design {8}

This PROCESS trial is a multicentric, randomized, open-label, blinded-endpoint study, designed to evaluate whether premedication with duloxetine within 72 h after VZV reactivation has a promising preventive effect on PHN. In total, 750 participants will be recruited from 18 different hospitals all over China. Participants will be assigned to either the duloxetine arm or the control arm in an allocation ratio of 1:1. The timeline and detailed schedule of the study are illustrated and summarized in Fig. 1.

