### Strategies to improve adherence to interventions {11c}

Once assigned to one of the two study groups, a pharmacological protocol will be given as per allocation. Physicians and research assistants will be responsible for instructing participants to follow the protocols correctly, and to ensure adherence to interventions. After recruitment, each participant will be given a pain diary (PD), in which all outcomes can be recorded by the participants themselves during the study period. The specific recording criteria are as follows: (i) the VAS score will be recorded every morning before breakfast, (ii) AEs and consumption of each analgesic will be recorded every evening before bed, and (iii) the 12-item Short-Form Health Survey (SF-12), Patient Global Impression of Change Scale (PGIC) and Sleep quality as measured by the Pittsburgh Sleep Quality Index (PSQI) will be self-assessed at baseline and upon completion of weeks 4, 8, and 12. During the study period, the research assistants will monitor the participants’ completion of the PDs and deliver reminders as necessary through telephone calls or social media. At the end of week 12, the PDs will be collected by the research assistants and stored by the Data Safety Monitoring Board (DSMB). The research assistants will be available 24 h a day, 7 days a week, to answer any questions related to the study.

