### Assignment of interventions: blinding

#### Who will be blinded {17a}

Only the outcome assessors and data analysts will be blinded to the study.

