### Data collection and management

#### Plans for assessment and collection of outcomes {18a}

Research assistants will gather the patients’ baseline demographic characteristics searching the institutional electronic medical records or asking participants directly. The baseline and outcomes for the intervention will be compared to the control arm for primary analysis. After recruitment, each participant will be given a PD, in which all outcomes can be recorded by the participants themselves during the study period. The specific recording criteria are as follows: (i) the VAS score will be recorded every morning before breakfast, (ii) AEs and consumption of each analgesic will be recorded every evening before bed, and (iii) the SF-12, PGIC and PSQI will be self-administered at baseline and upon completion of weeks 4, 8 and 12. During the study period, the research assistants will monitor the participants’ completion of the PDs and deliver reminders as necessary through telephone calls or social media software. At the end of week 12, the PDs will be collected by the research assistants and stored by the DSMB. An investigator will sample every participant file and check for missing data.

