
This study has several limitations. An open-label design instead of a blinded, placebo-controlled design will be used in this nationwide multicentric study due to limited funding support. Although an open-label trial [34] reflects real clinical circumstances more effectively than a blinded trial and maintains the advantages of randomized allocation and blinded outcome assessors, the therapy recommended for the control arm can be considered an active control, as the intervention of duloxetine involves an add-on therapy, the effect of placebo may not be well perceived. As a result, VAS in the duloxetine arm may be underestimated; however, limited impact on primary outcome is assumed as any pain score other than 0 on the VAS at 12 weeks after HZ onset will be established as PHN. Although lower VAS is expected for the duloxetine arm, the incidence of PHN may not be significantly influenced by the absence of placebo. Even so, randomized, blinded, placebo-controlled clinical trials are needed. The study period in this trial is limited to 12 weeks; consequently, little is revealed about the long-term preventive effectiveness of duloxetine. Similarly, the maximum dosage of duloxetine was set at 60 mg per day, and this study does not address whether a higher dosage would have a more significant advantage or what dosage is optimal in the prevention of PHN. For safety reasons, immunosuppressed patients will not be included in the current study. Further investigation is needed for that population.

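### The trial is labelled blinded-endpoint, but participants who know their arm score the primary VAS themselves, and the argument that a cut at 0 mm limits the resulting bias is unsupported

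*Protocol article*

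**What the plan says.** **Label.** Trial design {8} describes a "multicentric, randomized, open-label, blinded-endpoint study". The same label stands in the Abstract (Methods), Background and rationale {6a}, Study setting {9} and the opening of the Discussion.

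**Who is blinded.** Sequence generation {16a} says that "the patients, physicians and research team will inevitably be aware of the allocation", and continues: "However, the outcome assessors will be blinded to the intervention". Who will be blinded {17a} states: "Only the outcome assessors and data analysts will be blinded to the study". Concealment mechanism {16b} and Procedure for unblinding {17b} repeat this, and the limitations part of the Discussion counts blinded assessors among the strengths that the design keeps.

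**Who scores.** Strategies to improve adherence {11c} says that "each participant will be given a pain diary (PD), in which all outcomes can be recorded by the participants themselves during the study period". Plans for assessment and collection of outcomes {18a} repeats this and adds that "the VAS score will be recorded every morning before breakfast".

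**How the score becomes the endpoint.** Under Outcomes {12}, any VAS value other than 0 mm at 12 weeks after onset counts as PHN.

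**The stated defence.** The limitations paragraph concedes that VAS in the duloxetine arm may be underestimated without a placebo, but says "limited impact on primary outcome is assumed as any pain score other than 0 on the VAS at 12 weeks after HZ onset" defines PHN, and concludes that PHN incidence may not be materially affected.

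**The concern.** A blinded endpoint protects a trial when someone unaware of allocation makes the judgement that decides the outcome. Here the judgement is the participant's own mark on the VAS line, and the participant knows the arm. Blinding whoever later reads the diary cannot blind the mark already in it.

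The argument about the cut at 0 mm was meant to close this gap. If it fails, the endpoint is open to differential reporting and the article tells readers otherwise. At stake is how a positive result may be read: as prevention, or as prevention mixed to an unknown degree with expectation. The label stands in the Abstract, where it is most likely to be taken at face value.

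**Working it through.** **1. Label against data flow.**

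| Step towards the primary endpoint | Who acts | Knows the arm? | Source |
|---|---|---|---|
| Marks the daily VAS | Participant | Yes | {11c}, {18a}; {16a} |
| Monitors the diary, sends reminders | Research assistants | Not described as blinded; the research team is said to know the allocation | {11c}, {18a}, {18b}; {16a} |
| Turns VAS into PHN or not | Fixed rule, 0 mm or not | No judgement involved | {12} |
| Compares the arms | Analysts | Blinded | {16b}, {17a} |

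No step is described in which a blinded person forms the VAS score or adjudicates PHN.

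**2. Does a cut at 0 mm protect the endpoint?** Suppose knowledge of treatment lowers a score by a few millimetres. A participant at 50 mm remains a PHN case. A participant at 3 mm who marks 0 becomes a non-case. So the cut protects against shifts in high scores and not against shifts in scores just above 0. Whether the net effect is small depends on how many week-12 scores lie near 0, which the article does not report.

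**3. Sensitivity of the primary test (illustration).** The plan gives no figure for this bias, so there is none to reproduce.

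Inputs from Sample size {14}, Sequence generation {16a} and Statistical methods {20a}: 750 participants, 1:1, 15% loss, control rate 30%, chi-squared test, two-sided alpha 0.05.

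- Evaluable per arm: n = 750 × 0.85 / 2 = 318.75, about 319.
- Assumption: the drug does nothing, so true PHN is 30% in both arms.
- Assumption: a share m of duloxetine-arm cases mark 0. The observed rates are p1 = 0.30 and p2 = 0.30 × (1 − m), with d = p1 − p2 and p̄ = (p1 + p2)/2.
- SE0 = √(2p̄(1 − p̄)/n); SE1 = √((p1(1 − p1) + p2(1 − p2))/n); c = 1.96 × SE0.
- P(reject) = Φ((d − c)/SE1) + Φ((−d − c)/SE1).

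Worked case, m = 10%: p2 = 0.27, d = 0.03, SE0 = 0.03576, SE1 = 0.03574, c = 0.0701. Then Φ(−1.122) + Φ(−2.800) = 0.131 + 0.003 = 0.134.

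| Share m marking 0 | Patients (n × 0.30 × m) | Observed duloxetine rate | P(false positive) |
|---|---|---|---|
| 0% | 0 | 30.0% | 5.0% |
| 5% | 4.8 | 28.5% | 7.0% |
| 10% | 9.6 | 27.0% | 13.4% |
| 20% | 19.1 | 24.0% | 40.0% |
| 33% | 31.9 | 20.0% | 83.2% |

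The last row is the planned contrast, 30% against 20%, produced by reporting alone. A separate simulation of 400,000 comparisons gave 0.134, 0.399 and 0.832 for 10%, 20% and 33%.

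**4. The same question in counts (319 per arm, pooled z).**

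- From equal arms, 96 cases each, 22 changed marks in the duloxetine arm (96 against 74) give z = 1.97.
- If the trial observed the planned rates, 96 against 64 cases, then z = 2.92. Reclassifying 10 duloxetine-arm zeros as cases (96 against 74) leaves z = 1.97; reclassifying 11 (96 against 75) gives z = 1.88 and significance is lost. That is 11 of 319 − 64 = 255 zero marks, or 4.3%.

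**The case against.** **Disclosure.** The article is open about much of this. Every design label includes the word open-label, {16a} and {16b} say that patients know their arm, and the limitations paragraph concedes a possible shift in VAS and calls for blinded placebo-controlled trials. This stands, and a careful reader could work out the true position. It does not make the label correct, because the same paragraph still claims blinded assessors as an advantage.

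**Size of the bias.** A reader might infer that the cut at 0 mm makes the bias large, or that a positive result would be nothing but reporting bias. The documents support neither. They give no distribution of week-12 scores. If residual scores were spread evenly over 1 to 100 mm (an assumption), a 5 mm shift would move about 5% of cases, and the false-positive rate would be about 7%, near nominal. Scores could cluster lower, but that is unknown. The 33% row is an extreme with no support in the article.

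**Role of the assessors.** A reader might also infer that nobody assesses anything in this trial. That goes too far. The section on the trial steering committee {5d} has that committee assess adverse events and their relation to study drugs, and mentions an operation manual and forms that are not shown. Table 1 and Fig. 1 were not available either. The point is therefore limited to the self-scored outcomes as the text describes them.

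**Supportive analyses.** A non-zero VAS cut-off uses the same unblinded self-score, and scores near any other cut can also cross it. Analgesic use is not independent evidence: under {11d} it stops once VAS is 0, and it is recorded in the same diary. These objections stand. Agreement of such analyses should not be a condition for claiming prevention.

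**Conclusion.** The concern holds in a limited form. On the article's own text, the primary endpoint is an unblinded self-report converted by rule, so neither the blinded-endpoint label nor the assessor-blinding statements describe a property that this endpoint has. The analysts' blinding is real and should stay.

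The defence based on the 0 mm cut does not follow from the concession before it and has no data behind it. That is weaker than saying the reverse has been shown.

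The size of the bias cannot be derived. Over assumed shares of 5% to 33%, the false-positive rate runs from about 7% to 83%, given 30% true PHN in both arms, about 319 evaluable per arm and misreporting in the duloxetine arm only. These figures show sensitivity and do not predict what will happen.

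**What to change.** 1. **Label.** Replace blinded-endpoint with: open-label, participant-reported primary outcome, analysts blinded. This applies to the Abstract (Methods), Background and rationale {6a}, Trial design {8}, Study setting {9} and the opening of the Discussion.
2. **Assessor blinding.** In {16a}, {16b}, {17a}, {17b} and the limitations paragraph, withdraw the assessor-blinding claim for self-reported outcomes. Edit these sentences and do not delete them whole, because {16b}, {17a} and {17b} also carry the analysts' blinding.
3. **Limitations paragraph.** Replace the two reassurances, on the primary outcome and on PHN incidence, with a statement that the primary outcome is open to reporting bias of unknown size.
4. **One supportive analysis of the existing diary data.** For example, a tipping-point analysis of how many duloxetine-arm zero scores would have to be reclassified as PHN before significance is lost, or a repeat of the comparison at a non-zero VAS cut-off. Label it as a check of robustness at the zero boundary. It does not remove the bias and is not a condition for success.

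The cost is a less favourable design label and one extra analysis. Data collection, visits and the primary test stay as they are.

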#### Concealment mechanism {16b}

Since this is an open-label study, the patients, physicians and research team will inevitably be aware of the allocation. However, the outcome assessors and statistical analysts will be blinded to the intervention.

#### Implementation {16c}

An experienced research investigator, not involved in any other aspect of the study will use a web-based central randomization system with permuted blocks, to assign the patients in either the duloxetine arm or the control arm in a 1:1 ratio. Participants who fulfil the eligibility criteria will be enrolled in the study by the research assistants assigned for recruitment.

### Assignment of interventions: blinding

#### Who will be blinded {17a}

Only the outcome assessors and data analysts will be blinded to the study.

#### Procedure for unblinding if needed {17b}

This is an open-label study with only the outcome assessors and data analysts being blinded. Therefore, unblinding will not occur.

### Data collection and management

#### Plans for assessment and collection of outcomes {18a}

Research assistants will gather the patients’ baseline demographic characteristics searching the institutional electronic medical records or asking participants directly. The baseline and outcomes for the intervention will be compared to the control arm for primary analysis. After recruitment, each participant will be given a PD, in which all outcomes can be recorded by the participants themselves during the study period. The specific recording criteria are as follows: (i) the VAS score will be recorded every morning before breakfast, (ii) AEs and consumption of each analgesic will be recorded every evening before bed, and (iii) the SF-12, PGIC and PSQI will be self-administered at baseline and upon completion of weeks 4, 8 and 12. During the study period, the research assistants will monitor the participants’ completion of the PDs and deliver reminders as necessary through telephone calls or social media software. At the end of week 12, the PDs will be collected by the research assistants and stored by the DSMB. An investigator will sample every participant file and check for missing data.

#### Plans to promote participant retention and complete follow-up {18b}

Each participant will be given a PD, in which all outcomes can be recorded by the participants themselves throughout the study period. The research assistants will be available 24 h a day, 7 days a week, to answer any questions related to the study. During the study period of 12 weeks, the research assistants will monitor the participants’ completion of the PDs and deliver reminders as necessary through telephone calls or social media software.

#### Data management {19}

The institutional data monitoring committee will serve as the DSMB and be responsible for data safety. The study protocol will be sent to the DSMB before the initiation of the study. During the study period of 12 weeks, the research assistants will monitor the participants’ completion of the PDs. At the completion of 12 weeks, a data quality audit will be performed. All PDs collected will be stored in a secure location by the lead investigators, undisclosed to other research members.

#### Confidentiality {27}

Throughout the duration of the study, all patient data will be recorded and stored in a locked cabinet by the lead investigator. Patient information will be kept confidential and only the lead investigator of each assigned centre will have access to the files corresponding to the personal data of the respective participants.

#### Plans for collection, laboratory evaluation and storage of biological specimens for genetic or molecular analysis in this trial/future use {33}

This study does not involve collecting, laboratory evaluation or storage of biological specimens for genetic or molecular analysis for future use.

### Statistical methods

#### Statistical methods for primary and secondary outcomes {20a}

Statistical analyses will be performed using the SPSS 25.0 software package for Windows (SPSS, Inc., Chicago, IL, USA). The baseline and outcomes for the intervention will be compared to the control arm for primary analysis. Continuous variables will be expressed as the mean (SD) or median (IQR) and compared using Student’s *t* test or the Mann-Whitney *U* test. Normality will be tested using the Kolmogorov-Smirnov test. Categorical variables will be expressed as the number of patients (percentage) and compared using the chi-squared test or Fisher’s exact test. A 2-tailed alpha of 0.05 will be used as the threshold of statistical significance. The incidence of PHN in each arm at the end of week 12 will be compared using the chi-squared test. Subgroup analyses will be performed for age, gender, time to medication, maximum duloxetine dosage and average weekly pain score. Multiple logistic regression will be used to evaluate and determine the interference of the above confounding factors in the primary outcome. All analyses will be performed using both the intention-to-treat and per-protocol principles, and the final conclusion will be determined in line with the intention-to-treat principle.

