**Methods:**

This is a nationwide multicentric, randomized, open-label, blinded-endpoint study that will recruit 750 participants from 18 primary centres in China. Patients aged more than 50 years who are diagnosed with uncomplicated HZ, present with vesicles within 72 h of their emergence, and have an average pain score of at least 40/100 mm on a visual analogue scale (VAS, 0 mm = no pain, 100 mm = worst possible pain, at opposite ends of a 100-mm line) will be recruited for this study. Participants will be randomized into a duloxetine arm and a control arm. Participants allocated to the duloxetine arm will be given antivirals, analgesics and duloxetine, while those allocated to the control arm will receive antivirals and analgesics but no duloxetine. The primary outcome of this study is preventive efficacy against PHN, which will be evaluated based on a 100 mm VAS. Any pain scores other than 0 mm on the VAS 12 weeks after HZ onset will be defined as PHN. The secondary outcomes will consist of the average weekly VAS score, the average weekly consumption of each analgesic, weekly feature of the pain, patients’ quality of life based on the 12-item Short-Form Health Survey, Patient Global Impression of Change Scale, sleep quality as evaluated by the Pittsburgh Sleep Quality Index and adverse events during the study period.

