### Eligibility criteria {10}

Patients presenting to the Department of Emergency, Dermatology, Neurology or Pain Management at any participating centre will be screened for eligibility to join the present study. Patients aged more than 50 years who are diagnosed with uncomplicated HZ, present with vesicles within 72 h of their emergence, and have an average pain score of at least 40/100 mm on a visual analogue scale (VAS, 0 = no pain, 100 = worst possible pain, at opposite ends of a 100-mm line) will be considered to fulfil the inclusion criteria. Patients who refuse to participate in the study or to provide written informed consent; those who have a raw score of more than 50 points on the Zung Self-Rating Depression Scale [26]; those who are confirmed to have HZ with head, neck, ocular, mucous membrane, cranial nerve, or central nervous system involvement or generalized HZ; those who are observed to have haemorrhagic or necrotizing lesions, satellite lesions, abnormal vesicles or acute retinal necrosis; those who have been on immunosuppressive therapy or mono- or multi-pharmacotherapy that involves any tricyclic antidepressant, valacyclovir, duloxetine or cytotoxic medications before acute HZ onset; those who have been diagnosed with hepatic, renal or immune dysfunction; those who are pregnant or breastfeeding; those with recorded hypersensitivity to the study drugs; those with contraindications to valacyclovir or duloxetine; and those who have been immunized with the HZ vaccination will be excluded from the study. Prior to the initiation of this study, research assistants (at least 2 research assistants per centre) will be trained regarding the details of this study protocol to ensure that the work would proceed smoothly. When patients are identified and diagnosed with acute HZ, research assistants will be informed and asked to screen the patients for eligibility. Eligible patients who are willing to participate will be recruited for the study.

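### Repeated secondary outcomes (weekly VAS, SF-12, PSQI) are compared by unadjusted two-sample tests, with no use of baseline and no lead time point

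*Protocol article*

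**What the plan says.** The section on statistical methods for primary and secondary outcomes {20a} sets one rule for every continuous variable: "Continuous variables will be expressed as the mean (SD) or median (IQR) and compared using" Student's t test or the Mann-Whitney U test. The pre-test is named in the next sentence: "Normality will be tested using the Kolmogorov-Smirnov test". The error level is common to all tests: "A 2-tailed alpha of 0.05 will be used as the threshold of statistical significance".

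The outcomes under this rule are longitudinal. The abstract and the secondary outcomes list include the "average weekly VAS score", and the data collection section {18a} says that "the VAS score will be recorded every morning before breakfast" over the 12-week study. For the questionnaires, the same section says that "the SF-12, PGIC and PSQI will be self-administered at baseline and upon completion of weeks 4, 8 and 12"; the adherence section {11c} gives the same schedule. An entry pain value is also known, because patients must "have an average pain score of at least 40/100 mm on a visual analogue scale" (Eligibility criteria {10}).

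Section {20a} says that baseline will be compared between arms. It does not say that baseline enters any comparison of continuous outcomes. The only regression named, in {20a} and {20b}, is logistic and serves the primary binary outcome.

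**The concern.** Student's t and Mann-Whitney take one value per participant and no covariate. Applied to an outcome measured at 3 or 12 time points, with no summary measure and no lead time point named, they lead to one p-value per time point.

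Two things are at stake. The first is interpretation. About 18 unranked p-values at 0.05 leave open which one carries the conclusion for each outcome. In an open-label trial with self-recorded diaries, a favourable week can be singled out afterwards. The second is precision. Baseline values that are already being collected are left out of the comparison.

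The normality switch adds a smaller problem. The type of summary and test would be chosen from the data, and could differ from week to week for the same outcome.

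**Working it through.** The documents give no figure of their own on this point, so there is none to reproduce. They give no correlations either; those below are assumptions, shown as ranges.

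**Number of tests.** Weekly VAS over 12 weeks gives 12. SF-12 and PSQI at weeks 4, 8 and 12 give 3 each. The total is 12 + 3 + 3 = 18. Scoring SF-12 as two components would make it 21, and weekly analgesic consumption would add more.

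**False positives under the null.**
- Expected number: 18 × 0.05 = 0.9.
- At least one among the 12 VAS tests, if independent: 1 − 0.95^12 = 0.46.
- At least one among all 18, if independent: 1 − 0.95^18 = 0.60.

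Weekly pain averages in the same patients are positively correlated, which lowers these figures. Simulating 12 correlated z-statistics (400,000 draws, each tested at two-sided 0.05) gives the chance of at least one false-positive week:

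| Assumed correlation | Decaying with lag, AR(1) | Equal between all weeks |
|---|---|---|
| 0.3 | 44% | 40% |
| 0.5 | 41% | 32% |
| 0.7 | 34–35% | 23% |
| 0.8 | 29% | 18–19% |
| 0.9 | 21% | 13% |
| 0.95 | 16% | 10.5% |

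The figure stays above 5% in every case tried, but at the high-correlation end it is far below the independence value.

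**Precision.** Linear adjustment for a baseline that has correlation ρ with the outcome multiplies the variance of the treatment contrast by 1 − ρ².
- ρ = 0.3: 1 − 0.09 = 0.91, a 9% reduction.
- ρ = 0.5: 1 − 0.25 = 0.75, a 25% reduction.

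Sample size {14} gives 750 participants and 15% loss, so 750 × 0.85 = 637.5 evaluable, or 318.75 per arm. In equivalent unadjusted sample size, adjustment is worth 637.5/0.91 ≈ 701 or 637.5/0.75 = 850 evaluable participants. A contrast with 80% power unadjusted has (1.960 + 0.842) ≈ 2.80 standard errors of signal. After adjustment its power is Φ(2.80/√0.91 − 1.96) ≈ 83.6% or Φ(2.80/√0.75 − 1.96) ≈ 89.9%.

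**The normality pre-test late in the trial.** PHN is defined as any non-zero VAS at 12 weeks, and Sample size {14} assumes 30% and 20% incidence. On those assumptions 70% to 80% of participants score exactly 0 at week 12, and the last weekly averages will be similarly heavy at zero. The empirical distribution then jumps by at least 0.70 at a single point, so its greatest distance from any continuous curve is at least 0.70/2 = 0.35. The approximate 5% critical value with 319 in an arm is 1.36/√319 = 0.076. The pre-test is then certain to reject, so at that point it does not inform the choice. With more than half the values at zero, the median is 0 in both arms.

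**The case against.** The strongest reply is that {20a} is one generic sentence in a condensed article. It nowhere says that every week is tested separately, and time points, covariates and multiplicity for secondary outcomes are commonly left to an analysis plan. It is true that separate weekly tests are an inference. But the article does not simply stay silent: it names the test family, and that family takes one value per participant with no covariate. A baseline-adjusted model would replace the stated method, not merely fill it in.

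Some stronger readings are tempting, and the documents do not support them:
- A reader might infer that ignoring correlation over time inflates type I error. It does not. A two-sample test at one week compares different people and holds its 5% level. The false positives come from the number of unranked tests, and positive correlation reduces the family-wise rate.
- A reader might infer that each week is analysed on complete cases, so that the population shifts. No passage specifies that. Section {20c} commits to intention to treat and expects no missing data; whether that is realistic is a separate question.
- A reader might infer that no effect size will be reported. Per-arm means (SD) or medians (IQR) are planned. What the stated tests do not supply is a baseline-adjusted between-arm contrast.
- A reader might infer bias. Unadjusted comparison is unbiased under randomisation; what is lost is precision.

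It also stands that the gain for VAS is uncertain, since the 40 mm entry cut narrows the baseline range and may weaken its correlation with later scores. A Gaussian mixed model is not an obvious choice for VAS data with many zeros.

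**Conclusion.** The concern holds for secondary outcomes and is moderate in size. The stated method uses no baseline and designates no lead comparison for weekly VAS, SF-12 or PSQI. On the natural reading of one test per time point, the chance of at least one false-positive VAS week is about 10.5% to 44% for assumed correlations of 0.95 to 0.3; 46% is a ceiling that needs independence. The forgone variance reduction is 9% to 25% for an assumed baseline correlation of 0.3 to 0.5, possibly less for VAS. Both ranges rest on assumed correlations. The primary conclusion, a single chi-squared test of PHN at week 12, is not touched.

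**What to change.** For each of weekly VAS, SF-12 and PSQI, replace the switch between t and Mann-Whitney with a baseline-adjusted analysis: ANCOVA, or a repeated-measures mixed model with arm, time, arm-by-time and the baseline value, using robust standard errors. Prespecify one between-arm contrast per outcome (week 12, or the 12-week average for VAS), report it with a 95% CI, and show the other time points descriptively. Drop the Kolmogorov-Smirnov pre-test as the means of choosing the analysis.

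This reduces the family from about 18 tests to 3. If independent, those carry a chance of at least one false positive of 1 − 0.95³ = 14.3%, so the three remain supportive unless a multiplicity rule is added.

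The cost is a change of wording and slightly more analysis work, with no new data; SPSS, the named software, fits such models. The model assumptions need care for late VAS with many zeros. The 12-week average may be less affected than week 12 alone.
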